## Abstract

**Background:**

Interstitial lung disease (ILD) has a profound impact upon health-related quality of life (HRQoL) and mortality. Patients with ILD have identified their desire for tools to improve self-management. This study compares the clinical efficacy and cost-effectiveness of delivering an ILD-specific self-management package through a mobile health smartphone application (the REBUILD app), with standard care. It also evaluates the barriers and facilitators to adoption of the intervention in clinical practice.

**Methods:**

This is a prospective, multicentre, randomised control trial (RCT) with embedded economic and implementation evaluations, with recruitment via ILD clinics at four Australian tertiary hospitals. Participants are allocated 1:1 to intervention and control groups, with randomisation stratified by disease severity, diagnosis, and site. The intervention group receives the self-management package and four phone health coaching sessions over 12 weeks. The control group receives standard care and four phone calls to control for attention. Outcomes will be measured at 12, 26 and 52 weeks. The primary outcome is change in HRQoL at 12 weeks, measured by the King’s Brief Interstitial Lung Disease questionnaire.

**Discussion:**

Enhanced self-management has been associated with better HRQoL in several chronic respiratory conditions, however its effect in people with ILD is not known. This is the first multicentre RCT to evaluate the effect of a digital self-management intervention delivered through a smartphone app in people with ILD. If successful, this intervention has the potential to enhance access to self-management support for people with ILD.

**Trial registration:**

This project was prospectively registered with the Clinical Trial Registry (NCT06122233||https://www.clinicaltrials.gov//{08/11/2023}}.

## Background

The interstitial lung diseases (ILDs) are a group of chronic inflammatory and fibrotic lung disorders that share the symptomatology of worsening breathlessness, cough, impaired exercise tolerance, anxiety, and often extremely poor health-related quality of life (HRQoL) [1]. A global ILD prevalence of 6.3 to 71 per 100,000 and incidence of 1–31.5 per 100,000 person years have been reported, with estimates varying regionally due to heterogeneity of ILD categorisation methods [2]. The most prevalent form of fibrotic ILD is idiopathic pulmonary fibrosis (IPF), a severe and progressive lung disorder with median survival of only 2–5 years from diagnosis if left untreated [3]. Crude and age-standardised estimates of IPF incidence in Australia were recently reported as 10.4 and 11.2 per 100,000 population, respectively, while estimated age-adjusted mortality was 6.3 per 100,000 population – worse than for many cancers [4]. In Australia, an estimated $299 million is spent on IPF healthcare annually [5]. 

Idiopathic pulmonary fibrosis comprises approximately 30% of ILD in local and international cohorts [6, 7]. Increasing evidence shows other forms of fibrotic ILD share overlapping pathogenic and prognostic features, with common therapeutic targets. The antifibrotic drugs, nintedanib and pirfenidone, slow the deterioration of progressive fibrotic ILD [8–11], but do not improve HRQoL and in some cases, may contribute to worsening HRQoL through adverse effects [8, 9]. Holistic management strategies for people with ILD are desperately needed.

The 2019 Australian *National Strategic Action Plan for Lung Conditions* prioritised measures to support people with ILD, including improving self-management capabilities [12]. Self-management is an individual’s ability to manage the physical and psychosocial sequelae of living with a chronic condition, including symptoms, treatment, and lifestyle modifications, and implies a proactive involvement in one’s health [13]. Self-management has an established role in chronic obstructive pulmonary disease (COPD), asthma and cystic fibrosis [14, 15] and has been associated with improved HRQoL in these conditions. However, it is a relatively new concept in ILD with limited published data, although recognition of its importance is growing [16–18]. People with ILD report feeling a high level of responsibility for maintaining their health, and a strong desire for self-management [18–20]. An ILD self-management package was developed in partnership with ILD healthcare professionals and consumers, [17] with 12 components of a self-management program identified and confirmed by an independent Delphi consensus [21]. A recent randomised control trial (RCT) evaluated the feasibility of this package with positive results, [22] and an additional module, ‘Managing Weight and Nutrition,’ was incorporated based on participant feedback.

Mobile health or mHealth apps can facilitate self-management, leveraging widely available technology for broad reach. To date, mHealth apps used to support self-management have demonstrated positive effects on HRQoL in asthma, COPD, and cystic fibrosis, [23–25] however their impact in patients with ILD is unknown. Together with consumers engaged through the Centre of Research Excellence for Pulmonary Fibrosis (cre-pf.org.au) Consumer Advisory Group, our team designed and developed the REBUILD app, with a recent pilot study showing high user engagement and satisfaction with the intervention [26]. 

## Methods

### Study design and setting

The REBUILD-SM trial is a multicentre parallel-group RCT with embedded implementation and economic evaluations recruiting 400 people with ILD. It is expected to run from 2024 to 2027 and be conducted at four Australian tertiary hospitals currently participating in the Australasian ILD Registry (AILDR). Participant enrolment commenced in June 2024 with anticipated completion by December 2026.

### Participants

People with fibrotic ILD are eligible if they (i) are ≥ 18 years of age; (ii) can provide informed consent; (iii) have been on stable ILD treatment for the month preceding enrolment; (iv) own or have access to a smartphone or tablet to download the REBUILD app to; (v) have access to email; (vi) are able to understand written and spoken English; and (vii) have sufficient digital literacy as quantified by the ability to use a mobile phone, download new apps, and enter keywords into a search box [27]. Exclusion criteria includes (i) acute ILD exacerbation in the month preceding enrolment; (ii) participation in pulmonary rehabilitation at enrolment or; (iii) death or transplant expected within the 12 week intervention period.

### Recruitment and consent

Participants are recruited from ILD clinics at four sites and through the AILDR. Potential participants are approached by a healthcare professional in person or via phone and given information about the study. AILDR participants are sent a recruitment letter via post or email. A member of the research team will contact interested potential participants and those wishing to enrol will download the REBUILD app and complete the consent electronically.

### Randomisation, concealment of allocation and blinding

Participants are randomised via the app 1:1 to intervention or control group for the 12-week intervention period. Permuted block randomisation, stratified by (i) diagnosis of IPF or not; (ii) FVC of ≤ 50% or ≥ 51%; and (iii) study centre will occur upon entry of these factors. Participants failing to enter this data will not be randomised. The nature of the intervention makes blinding of participants and healthcare professionals delivering the intervention impractical; however, endpoint assessment will be blinded for outcome assessors and data analysts using a Prospective Randomised Open Blinded Endpoint (PROBE) [28] approach. This study is designed according to SPIRIT guidelines [29] and will be reported according to CONSORT standards [30]. 

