### Control group

The control group receive the same standard of clinical care as the intervention group, including regular ILD clinic reviews, meaning the medical management of both groups is the same. The control group also receive access to a reduced capability or ‘lite’ version of the REBUILD app for remote data collection and self-monitoring only. The lite version of the app does not include access to the educational materials or the self-management content but does include the physical activity and air quality features described above. To control for the effects of attention, participants in the control group will receive calls at the same frequency as the intervention group, however these calls will be general in nature with no health advice provided. Calls will be completed by site study coordinators, who will offer technical support only. Participants seeking health advice will be directed to their usual care providers.

At week 26, participants in the control group will receive access to the full version of the REBUILD app (Fig. 3) on ethical grounds, however this will not include access to the self-management package or the phone support provided in the intervention. This difference will be accounted for during the final data analysis.

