### Aims and outcomes

This study aims to compare the clinical efficacy and cost-effectiveness of the self-management package delivered through the REBUILD app to standard clinical care; and to understand the barriers and facilitators to adoption of the intervention. The study team hypothesise that REBUILD-SM will (1) improve HRQoL, symptoms, anxiety, self-efficacy, and physical activity in people with ILD; (2) be a cost-effective intervention compared to standard care; and (3) be implementable in clinical practice.

The primary outcome is change in HRQoL measured by change in King’s Brief Interstitial Lung Disease (K-BILD) questionnaire score at 12 weeks. The K-BILD has been chosen as a valid, ILD-specific measure of HRQoL with demonstrated responsiveness to interventions; [31] and this timepoint was selected based on evidence showing change in physiological variables at 12 weeks to be predictive of mortality and disease progression in IPF patients [32]. Pulmonary rehabilitation (commonly lasting between 8 and 12 weeks) has also demonstrated efficacy in improving short-term HRQoL in people with IPF, [33] suggesting that 12 weeks will be sufficient to observe a treatment effect.

The secondary outcomes are as follows (see also Table 1):

Change in K-BILD score from baseline at week 26 and 52; and change in EQ-5D-5L score from baseline at week 12, 26 and 52Change in General Self-Efficacy Scale (GSE) score from baseline at week 12, 26 and 52Change in Dyspnoea-12 score from baseline at week 12, 26 and 52Change in Hospital Anxiety and Depression Scale (HADS) score from baseline at week 12, 26 and 52Change in physical activity level from baseline at week 12 and 52Uptake or changes to ILD treatments, including clinical trial enrolment at week 12, 26 and 52Acceptability of the REBUILD app, evaluated utilising the mHealth App Usability Questionnaire (MAUQ) score at week 12, 26, and 52; and app analytics, including frequency the app and its individual features are accessed and used, total time of use and percentage of complete data enteredChange in eHealth and Literacy Scale (eHEALS) score from baseline at week 12 and 52Autonomy, which will be evaluated using the Healthcare Climate Questionnaire (HCCQ) at week 12

**Table 1 Tab1:** Study endpoints

**Data collection**	**Baseline**	**Week**			
		**12**	**26**	**38**	**52**
Demographic and clinical information	**X**		**X**		**X**
HRQoL (K-BILD & EQ-5D-5L questionnaire)	**X**	**X**	**X**		**X**

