### Data collection

Study endpoints are completed using the REBUILD app, with push notifications informing participants when they have tasks to complete. Reminders will be sent at 24 and 48 h to encourage data completion, followed by a reminder phone call from sites if data is still pending at 72 h. An additional phone call will be completed if the endpoints remain outstanding after 5–7 days. Step count over a 7-day period will be measured at baseline, week 12 and 52 using the StepWatch activity monitor (Modus Health, Washington DC, USA), a reliable and validated tool used in patients with chronic lung disease [34]. Information on Emergency Department (ED) presentations and hospitalisations as well as uptake and changes to ILD treatment and clinical trial enrolment will be gathered from the participants’ electronic healthcare record.

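### The blinded-assessor (PROBE) claim does not cover K-BILD and the other questionnaires, which unblinded participants complete themselves; it can cover analysts, StepWatch and health-record data

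*Protocol article*

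**What the plan says.** The section on randomisation, concealment and blinding makes two statements in one sentence. The first is a concession: "The nature of the intervention makes blinding of participants and healthcare professionals delivering the intervention impractical". The second is a claim: "endpoint assessment will be blinded for outcome assessors and data analysts using a Prospective Randomised Open Blinded Endpoint (PROBE" approach.

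Under Aims and outcomes: "The primary outcome is change in HRQoL measured by change in King’s Brief Interstitial Lung Disease (K-BILD) questionnaire score at 12 weeks". Under Data collection: "Study endpoints are completed using the REBUILD app, with push notifications informing participants when they have tasks to complete". When questionnaires are overdue, automated reminders at 24 and 48 hours are "followed by a reminder phone call from sites if data is still pending at 72 h", with one more call after 5–7 days.

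Under Control group, the arms differ visibly: "The lite version of the app does not include access to the educational materials or the self-management content". The attention control is that "participants in the control group will receive calls at the same frequency as the intervention group", but those calls carry no health advice: "Calls will be completed by site study coordinators, who will offer technical support only".

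Step counts come from a StepWatch monitor. Emergency visits, hospitalisations, treatment changes and trial enrolment come from the electronic health record. The limitations in the Discussion cover tertiary-centre recruitment, digital literacy and English-only materials. They do not mention unblinded self-report.

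**The concern.** In a PROBE design, treatment is open and the protection comes from an endpoint assessor who does not know the allocation. A self-completed questionnaire has no such separate person: the respondent makes the assessment. Participants here know their arm, and those in the intervention arm have been coached on goals and progress by an ILD professional. Hopes for the intervention, or disappointment at not receiving it, can affect the K-BILD answers directly.

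Analyst blinding protects choices made during analysis. It cannot remove a difference in reporting that is already in the recorded answers. A reader who takes the PROBE label at face value would credit the primary result with a protection it lacks, and the limitations do not correct that impression.

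**Working it through.** **1. Who assesses each outcome, from the article's own text**

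| Outcome | Recorded by | Can assessment be blinded? |
|---|---|---|
| K-BILD (primary), EQ-5D-5L, GSE, Dyspnoea-12, HADS | Participant, in the app | No: participants are conceded to be unblinded and no other rater is described |
| Steps per day | StepWatch monitor | Yes, for data processing |
| Emergency visits, hospitalisations, treatment changes, trial enrolment | Extraction from the health record | Yes, if extractors are kept unaware of allocation |
| Statistical analysis of all outcomes | Data analysts | Yes |

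The claim fails for the first row and can stand for the other three.

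**2. The article's own precision figures**

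Inputs from the sample size section: 400 participants randomised equally (200 per arm); up to 15% missing endpoint data, leaving 200 × 0.85 = 170 per arm; a 5-unit difference, which is also the stated MCID; SD 15.6 in the first scenario and 6.5 in the second (printed with a percent sign, read here as K-BILD points). The Data analysis section gives a two-sided 5% level.

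Standard error of the difference = SD × √(2/n), with √(2/170) = 0.1085.

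- SD 15.6: SE = 1.692. Power for 5 points = Φ(5/1.692 − 1.96) = Φ(0.995) = 84.0% (83.8% by the t test). The stated figure of at least 82% is reproduced, so 170 per arm is a fair basis.
- SD 6.5: SE = 0.705.

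**3. Observed difference that just reaches significance, 1.96 × SE**

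- SD 6.5: 1.96 × 0.705 = 1.38 points; 1.38/5 = 28% of the MCID.
- SD 15.6: 1.96 × 1.692 = 3.32 points; 3.32/5 = 66% of the MCID.

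**4. Illustration of sensitivity to a reporting difference**

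Suppose the true effect is zero and answers differ between arms by b points through reporting alone. The value of b is an assumption; the article gives none. The probability of a significant result is Φ(b/SE − 1.96) + Φ(−b/SE − 1.96).

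| Assumed b (points) | SD 15.6 | SD 6.5 |
|---|---|---|
| 0 | 5.0% | 5.0% |
| 0.5 | 6.0% | 10.9% |
| 1 | 9.1% | 29.4% |
| 2 | 21.9% | 81.0% |
| 3 | 42.6% | 98.9% |

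Steps 3 and 4 describe the precision of the trial and what an assumed bias would do at that precision. They do not estimate the bias.

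**The case against.** The strongest reply is that the article does not conceal anything. It says in the same sentence that participants are unblinded, it never calls K-BILD itself blinded, and it claims blinding only for assessors and analysts. An unblinded patient-reported primary endpoint may be unavoidable for a self-management intervention. The control arm has the same number of calls, a self-monitoring app and the same route of endpoint collection. All of this stands, and it narrows the point to a general label that does not fit the primary endpoint. The matched calls address attention. They do not hide the reduced app or the absence of coaching.

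Four stronger readings are tempting and are not supported:

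- **A reader might infer that the trial has no blinded assessment at all.** Analyst blinding applies to K-BILD too, and StepWatch and record data can meet PROBE.
- **A reader might infer that site staff influence the answers**, since sites chase overdue questionnaires and site coordinators make the control calls. The reminder calls are described as prompts for completion. Nothing says that staff administer or score K-BILD, or that the procedure differs by arm. Whether the callers know the allocation is not stated, and an article may leave that to the full protocol.
- **A reader might infer that a bias of about 1.4 points is likely or would be decisive.** That figure is a significance threshold at the smaller of two stated SDs; the other gives 3.3. Neither measures bias.
- **A reader might infer that a K-BILD gain without more steps should be discounted.** Quality of life can improve without more walking, the article gives no power for steps, and an unblinded wearer still controls the behaviour that the monitor records.

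**Conclusion.** The point holds in limited form. Blinded outcome assessment is claimed in general terms but is not a property of the primary endpoint or of the other self-completed questionnaires. This follows from the article's statements on blinding, the primary outcome and data collection. It rests on one reading: that the participant alone rates K-BILD, since no independent rater is described.

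The size of any resulting bias is unknown. The thresholds of about 1.4 points (SD 6.5) and 3.3 points (SD 15.6) at 170 per arm show only that a reporting difference well below the 5-point MCID could matter, more so if the smaller SD is right. No estimand, test or sample size is wrong because of this. What needs correcting is the description of the design and the strength of the conclusion it is used to support.

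**What to change.** - Limit the PROBE statement to StepWatch data, record-extracted outcomes and data analysts.
- State that K-BILD, EQ-5D-5L, GSE, Dyspnoea-12 and HADS are self-reports by unblinded participants.
- Add this to the limitations, mention the attention-matched calls as partial mitigation, and word the interpretation of a positive K-BILD result accordingly.
- Report the already planned baseline-to-week-12 StepWatch comparison beside the K-BILD result as objectively measured supportive evidence, without making it a condition for the K-BILD conclusion.

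The cost is a change of wording. No new data are needed, because steps are already collected at week 12 and their comparison is already described. The downside is that the stated strength of the primary result becomes slightly less favourable. Enrolment has begun, so the change is most credible if made before any results by arm are known.

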### Intervention – self-management package

In addition to standard care, the intervention group will receive access to the ILD self-management content, four health coaching support phone calls, and the full version of the REBUILD app including educational resources. While the intervention is designed to improve the ability of participants to self-manage their disease, it is not intended to replace clinical care for either group. Both groups still attend their regular ILD clinic reviews and are managed according to usual care pathways by their treating team.

The intervention group can access the self-management package via *pflivingwell.com* and the REBUILD app (Fig. 1). The content includes 13 modules, organised by topic, each providing key information and embedded hyperlinks to relevant website, factsheet, booklet, video, and webinar resources vetted by our research team. The intervention is designed to improve self-management through information and activities related to goal setting, symptom tracking, self-reflection and problem-solving, compared with self-monitoring through the app alone [22]. Prior to accessing the self-management content, the intervention group complete an online introduction to identify which modules best align with their personal concerns and goals. Participants are then encouraged to review these modules throughout the intervention period.

**Fig. 1 Fig1:**
[figure not shown]
REBUILD-SM self-management modules

### Health coaching support calls

The intervention group will receive health coaching via phone or video call at 4 time points (week 1, 2, 3 and once between week 6 and 12) during the study period, with the aim of promoting engagement with the self-management modules. Calls will be made by an ILD healthcare professional who, throughout the intervention period, may provide support such as (i) guidance in identifying appropriate modules; (ii) assisting the participant to set health-related goals and identify strategies to achieve these; (iii) monitoring progress; (iv) addressing challenges; and (v) providing feedback or clinical recommendations. These calls also provide an opportunity for the healthcare professional to assess the participants’ understanding and tailor support accordingly. The outcomes of each session will be documented.

### The REBUILD app

The REBUILD app is designed to be a self-monitoring tool for both intervention and control group participants and is available for iOS and Android devices. It includes four sections: ‘Measurements’; ‘Your Tracking’; ‘Your Diaries’; and ‘Other Information.’ Various app screens are shown in Fig. 2. Participants in both groups will receive all sections, however only the intervention group will be able to view all components of ‘Other Information.’

**Fig. 2 Fig2:**
[figure not shown]
REBUILD app screens

#### Measurements

In this section, participants can enter their lung function test values (FVC and DLCO) and resting blood oxygen saturation (Sp0_2_) levels after obtaining this information from their ILD clinic assessment. Weight can also be recorded here, and participants are instructed to update this section when new results become available. Values are displayed graphically in the app to show trends over time.

